# Utility of a Machine-Guided Tool for Assessing Risk Behavior Associated With Contracting HIV in Three Sites in South Africa: Protocol for an In-Field Evaluation

**DOI:** 10.2196/30304

**Published:** 2021-12-02

**Keywords:** machine learning, predictive risk, modeling, algorithm, HIV status, HIV, risk assessment, South Africa

## Abstract

**Background:**

Mobile technology has helped to advance health programs, and studies have shown that an automated risk prediction model can successfully be used to identify patients who exhibit a high probable risk of contracting human immunodeficiency virus (HIV)*.* A machine-guided tool is an algorithm that takes a set of subjective and objective answers from a simple questionnaire and computes an HIV risk assessment score.

**Objective:**

The primary objective of this study is to establish that machine learning can be used to develop machine-guided tools and give us a deeper statistical understanding of the correlation between certain behavioral patterns and HIV.

**Methods:**

In total, 200 HIV-negative adult individuals across three South African study sites each (two semirural and one urban) will be recruited. Study processes will include (1) completing a series of questions (demographic, sexual behavior and history, personal, lifestyle, and symptoms) on an application system, unaided (assistance will only be provided upon user request); (2) two HIV tests (one per study visit) being performed by a nurse/counselor according to South African national guidelines (to evaluate the prediction accuracy of the tool); and (3) communicating test results and completing a user experience survey questionnaire. The output metrics for this study will be computed by using the participants’ risk assessment scores as “predictions” and the test results as the “ground truth.” Analyses will be completed after visit 1 and then again after visit 2. All risk assessment scores will be used to calculate the reliability of the machine-guided tool.

**Results:**

Ethical approval was received from the University of Witwatersrand Human Research Ethics Committee (HREC; ethics reference no. 200312) on August 20, 2020. This study is ongoing. Data collection has commenced and is expected to be completed in the second half of 2021. We will report on the machine-guided tool’s performance and usability, together with user satisfaction and recommendations for improvement.

**Conclusions:**

Machine-guided risk assessment tools can provide a cost-effective alternative to large-scale HIV screening and help in providing targeted counseling and testing to prevent the spread of HIV.

**Trial Registration:**

South African National Clinical Trial Registry DOH-27-042021-679; https://sanctr.samrc.ac.za/TrialDisplay.aspx?TrialID=5545

**International Registered Report Identifier (IRRID):**

DERR1-10.2196/30304

## Introduction

A recent study by Nguyen et al [1] showed that albeit the current progress achieved by some African countries in the effort to work toward reaching the Joint United Nations Programme on HIV/AIDS (UNAIDS) targets of human immunodeficiency virus (HIV) testing, the prediction shows little chance in achieving this by 2030. None of the African countries analyzed shows a high probability of achieving the targets; however, only three countries still have a chance of attaining this, with a probability below 50%. This may suggest that countries heavily affected by HIV may require substantial efforts, such as increased support from global organizations, to make progress toward the UNAIDS targets. Additionally, there is a need to find and make more effective changes in the previous strategies for encouraging behavioral interventions to increase condom usage, and strengthen HIV programs in many of the most affected countries. HIV-screening programs therefore are largely invested in preventing HIV transmission by promoting regular testing and continuous development of innovative prevention methods and messages [2,3]. Mobile technology has played a role in advancing health programs [4,5], and studies have shown that an automated risk prediction model can successfully be used to identify patients who exhibit a high probable risk of contracting HIV [6-8]. One of these studies demonstrates that with the use of machine-guided risk assessments, the process of pre-exposure prophylaxis (PrEP) initiation can become more efficient and suitable.

Although identifying persons who are at high risk of contracting HIV should enable a more targeted and cost-effective approach for prevention programs, universal screening programs are costly and labor intensive and do not have as high a success rate in identifying high***-***risk individuals [6,9].

Supervised learning is used to train machine learning models by using patient traits as inputs. There are two broad categories of patient traits:

Generic patient traits, such as age, gender, disease history, and moreDisease-specific traits, such as sexual behavior in the context of HIV

In the supervised learning paradigm, we need to know the ground truth to train the model, which in this case is a medical outcome, such as a diagnostic test result. The relationship between patient traits and outcomes can be analyzed by measuring the performance of the model [10,11].

A risk assessment tool is a set of simple and easy*-*to*-*understand questions *that* are answered by the participant(s)*,* and based on the responses, a risk probability is calculated. The questions are related to demographics, sexual behavior, sexual history, personal behavior, lifestyle*,* and medical history. The questions are scientifically designed based on the HIV correlation data from published research and clinical trials. The tool makes use of scientific algorithms to determine the risk probability and *provides* the outcome as low risk*,* medium risk*,* or high risk. Diagnostic assistive assessment is performed on a mobile device by the patients themselves*,* thus eliminating external influences and hence providing more accurate information.

In 2019-2020, a feasibility study was conducted with over 1000 participants at the Wits Reproductive Health and HIV Institute’s (WRHI) HIV self-testing assessment and research (HSTAR) Africa site in Johannesburg, South Africa. This study sought to understand the correlation between HIV status and factors such as demographics, sexual behavior and history, personal behavior and lifestyle, and symptoms, individually.

Analysis of the data collected from this feasibility study showed correlations between HIV status and all the variables. The main inference made was that patients can be grouped based on multiple factors as follows:

Primary features (demographics)Secondary features (lifestyle)Tertiary features (sexual behavior)Auxiliary features (symptoms)

Examples of the detailed analysis are shown in Figure 1.

**Figure 1 figure1:**
[figure not shown]
Examples of correlation between HIV status and selected features. Note: +1 shows a strong positive correlation, -–1 shows a strong negative correlation, and 0 shows no correlation between the variables. HIV: human immunodeficiency virus.

## Methods

### Objectives

The primary objective of this study is to assess the participants’ risk behavior using an automatic machine-guided tool and compare these results to HIV outcomes. The secondary objectives are:

To evaluate the participants’ interaction with the tool in terms of effectiveness and efficiency, that is, successful/unsuccessful completion and difficulty using the toolTo assess the ability of the participants to correctly comprehend and complete specific behavioral questions on a digital platformTo understand user experience and satisfaction with the overall process and recommend improvements for machine-guided tool development

The study is registered on the South African National Clinical Trial Registry (www.sanctr.gov.za; DOH-27-042021-679) and was approved by the University of Witwatersrand Human Research Ethics Committee (HREC; ethics reference no. 200312) on August 20, 2020.

### Design

In this longitudinal, supervised learning study, the data collected will be split into a training set and a validation set and the data used to validate the model will not be used in the training of the model, which will eliminate the need for a control group. This study will build on the feasibility study described before. The major variable shift is from a clinic-based setting to an in-field setting, which includes rural and semirural sites.

During the evaluation, the untrained user will be assessed thoroughly for process success or difficulty by a silent, non-interacting nurse/counselor. Overall, the process will include (1) completing a series of behavioral questions on an application system without the assistance of trained staff (assistance will only be provided on user request); (2) HIV testing being performed by the trained nurse/counselor (for comparator data to the risk assessment scores); and (3) communicating test results and completing a survey questionnaire developed to collect data on user experience.

All participants will have two rapid HIV tests performed. In the event of a positive HIV diagnosis, the participant will be referred for clinical treatment and care. If a participant tests negative, they will be found eligible for visit 2, which will occur 3 months after visit 1. At visit 2, the participant will follow the same process as that completed at visit 1 (Figure 2).

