### Study Site

Participants will be recruited from three districts situated in three provinces: (1) Tshwane, Gauteng; (2) Gert Sibande, Mpumalanga; and (3) Ugu, Kwa-Zulu Natal. The participating sites comply with all local government requirements for HIV testing and reporting. All sites will receive necessary approvals prior to enrolling participants.

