### Sample Size

A purposive sample of 600 participants across all sites (200 per site) will be recruited for this study. In machine learning, the required sample size for a study has not developed into a clear-cut methodology and requires data to compare model performance to relative data size. Therefore, the initial feasibility study maximized on available funding to determine an initial sample size for method validation and to allow for the ability to use the initial sample to compare the performance of the model to the sample size. As seen in Figueroa et al [12], 80-560 samples were required to reach a root-mean-square error below 0.01. A sample size of 600 based on the observations of Figueroa et al [12] will facilitate comparison between model sample size and model performance in order to inform further investigations and machine learning model development. As the device is intended to be used by both males and females from the general population, this assessment aims to recruit as close to a 50% breakdown per gender as possible.

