### Blinding of Results

This will be a blinded study. Participants will not be aware of their risk assessment scores. There will be no randomization of participants, as all participants will be required to interact with the machine-guided tool. This study will make use of supervised learning in which the data set will be collected and then used to train and test the machine learning model that has been created. The data will be collected in a specific area, and selection will be random. The data, however, will be split into training and validation data using a randomized split algorithm commonly found in statistical and data processing languages such as R and Python.

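### The random split puts every site in both training and validation, so the reported accuracy covers only sites the model was trained on; neither transfer to a new site nor the clinic-to-field shift is tested

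*Protocol article*

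**What the plan says.** All references are to the protocol article.

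- **Sample.** Sample Size states: "A purposive sample of 600 participants across all sites (200 per site) will be recruited for this study". Study Site adds: "Participants will be recruited from three districts situated in three provinces".
- **Validation.** Design says that "the data collected will be split into a training set and a validation set". Blinding of Results describes the data as "split into training and validation data using a randomized split algorithm commonly found in statistical and data processing languages such as R and Python". Sensitivity Analysis takes sensitivity, specificity and accuracy from the validation part of that split. No section holds out a site.
- **Second visit.** Under Design and Skewed Data, participants who test negative at visit 1 return after three months and their results are compared with the phase 1 model. These are the same people at the same sites.
- **Setting.** Design states: "The major variable shift is from a clinic-based setting to an in-field setting, which includes rural and semirural sites". The Methods paragraph of the Abstract describes the recruitment as "across three South African study sites each (two semirural and one urban) will be recruited".
- **Intended reach.** Study Population uses several regions to make the sample more representative of the general population. The Conclusion presents such tools as an alternative to large-scale screening.

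**The concern.** A random split answers one question: how well does the model predict for new people from the places that trained it? Two further questions matter for a tool meant for general use. Does it work at a site that gave no training data? Does a model built in a clinic still work in the field? The split described answers neither, because people from all three field sites are on both sides of it.

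There is also a route to flattering results. Race, education, occupation and working away from home are among the tool's questions (Subject Tool Evaluation). If undiagnosed HIV differs in prevalence between sites, these inputs can partly identify the site and gain accuracy from that alone. Such a gain need not carry over to a fourth site.

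At stake is how the result will be read. Good validation accuracy from a study titled an in-field evaluation is likely to be taken as evidence that the tool works in the field at large.

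**Working it through.** **1. The plan's own figure.** 3 sites × 200 = 600, as stated. The article gives no prevalence, power or precision target, so nothing else can be reproduced.

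**2. Can a site be missing from training?** The split fraction is not given, so a range is assumed. With n_v people in validation, the expected number from each site is n_v × 200/600. The 95% ranges are hypergeometric.

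| Split (assumed) | Training | Validation | Per site in validation (95% range) |
|---|---|---|---|
| 50/50 | 300 | 300 | 100 (89–111) |
| 70/30 | 420 | 180 | 60 (50–70) |
| 80/20 | 480 | 120 | 40 (31–49) |
| 90/10 | 540 | 60 | 20 (13–27) |

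A site is absent from training only if all 200 of its people fall in validation. At 50/50 the chance that this happens for any of the three sites is about 5 × 10⁻⁸³. It is exactly zero once validation holds fewer than 200 people. Stratifying the split by site would not help, since it places every site in both parts by construction.

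**3. Does visit 2 supply an unseen site?** No. It retests visit-1 negatives from the same three sites.

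**4. What would leave-one-site-out give?** Each rotation trains on 400 and tests on 200. Prevalence of undiagnosed HIV is assumed at 3% to 15% and sensitivity at about 80%; intervals are exact (Clopper-Pearson).

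| Assumed prevalence | Positives in held-out site | Detected | 95% interval |
|---|---|---|---|
| 3% | 6 | 5 | 36%–100% |
| 5% | 10 | 8 | 44%–97% |
| 10% | 20 | 16 | 56%–94% |
| 15% | 30 | 24 | 61%–92% |

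At 5%, the three held-out sites together contain 3 × 10 = 30 positives, and 24/30 gives 61%–92%. A 70/30 random split would hold 180 × 0.05 = 9 positives in validation, and 7/9 gives 40%–97%. The rotation scores all 600 people out of sample, so its combined interval is narrower, though that interval ignores variation between sites.

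The training size of 400 is below the upper end (560) of the range cited in Sample Size, but so are 420 (70/30) and 480 (80/20).

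**5. How much could site identity alone contribute?** Take a score that identifies the site perfectly and nothing else, with 200 per site. AUC is the share of positive–negative pairs in which the positive comes from the higher-prevalence site, counting same-site pairs as one half.

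- Prevalences 3/6/12% (assumed): positives 6, 12, 24; negatives 194, 188, 176. Numerator: 6 × 97 + 12 × (194 + 94) + 24 × (194 + 188 + 88) = 582 + 3,456 + 11,280 = 15,318. Denominator: 42 × 558 = 23,436. AUC = 0.65.
- Prevalences 4/5/6% (assumed): positives 8, 10, 12; negatives 192, 190, 188. Numerator: 8 × 96 + 10 × (192 + 95) + 12 × (192 + 190 + 94) = 768 + 2,870 + 5,712 = 9,350. Denominator: 30 × 570 = 17,100. AUC = 0.55.

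Within any one site the same score has AUC 0.50. For each set of prevalences the figure is a ceiling on what site identity alone adds, because site is not one of the tool's questions.

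**The case against.** **The study does not claim to test site transfer.** This is correct. The primary objective under Objectives is to compare tool results with HIV outcomes, and the shift named in Design is clinic to field, not one field site to another. A reader might infer that transfer between sites is what the study was set up to test; the article does not say so. Leave-one-site-out would also not test the clinic-to-field shift, which needs a model fixed before the field data are seen.

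**A random hold-out is ordinary internal validation at this stage.** This stands too. Its use is not an error. The difficulty lies in what may be concluded from it.

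**The risk scores themselves are compared with test results.** If the scores came from a model already fixed on the clinic data, that comparison would test the clinic-to-field shift. The article does not say which model produces the scores, and the performance measures it assigns to the model come from the split of the new data.

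**The inflation figures are hypothetical.** They are. The site prevalences are assumed, the inputs are only partial markers of site, and demographic differences may be genuine risk information. The article names confusion-matrix measures, not AUC.

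**Gender.** A reader might infer that genders are also recruited in fixed numbers and then mixed by the split. The text says only that "this assessment aims to recruit as close to a 50% breakdown per gender as possible". Gender has no bearing on the unseen-site argument, and reporting by gender or stratifying the split is detail that may sit in the analysis plan.

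**Held-out sites give imprecise answers.** True at low prevalence, and three sites say little about variation between sites. Wide intervals would show that uncertainty openly.

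**Conclusion.** The point holds as a limit on interpretation with an inexpensive remedy. Under the split described, every site is in both training and validation whatever split fraction is chosen, and visit 2 does not change this. The accuracy measured on the validation part therefore applies to the three sites used in training. It tests neither transfer to an unseen site nor the clinic-to-field shift.

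That conclusion rests on the article's text and the 200 per site, not on any assumed prevalence. How optimistic the result might be is unknown. The AUC range of 0.55 to 0.65 is for a perfect site marker under assumed prevalences of 4/5/6% to 3/6/12%, and should not be quoted as an estimate of bias.

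Separately, the descriptions of the sites do not agree: the Abstract has one urban and two semirural sites, whereas Design speaks of rural and semirural ones. Study Site lists the districts without settling it. This matters because it determines which settings any claim can cover.

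**What to change.** 1. Alongside the random split, report leave-one-site-out validation: train on two sites (400), test on the third (200), and rotate through all three. Give sensitivity and specificity for each held-out site and combined, with 95% intervals.
2. If this is not done, limit the conclusion to the three sampled sites.
3. If a model can be locked on the feasibility data (over 1000 participants, Introduction), apply it unchanged to the field participants. This is the direct test of the clinic-to-field shift. State which model produces each reported score.
4. Use one description of the sites throughout, and claim performance only for the settings actually included.

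**Cost.** No extra participants are needed, only additional model fits on the planned 600. Per-site intervals will be wide at low prevalence, and accuracy may look less favourable than under the random split. Item 3 depends on the feasibility data containing the same inputs, which the article does not establish.

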Unemployed (no job)When was the last time you tested for HIV?0-3 months3-12 monthsMore than 12 monthsNever testedDo you use a condom during sex?YesNoSometimesI have never had sex.Please select the gender and age of all sexual partners with whom you had sex in the past 3 months.Number of partners and age groups (Figure 4)No sex in the past 3 monthsWhich of the following sexual activities have you performed in the past 6 months?Anal receptive (you receive penis in anus)Anal insertive (you insert penis in partner’s anus)Vaginal receptive (you receive penis in vagina)Vaginal insertive (you insert penis in partner’s vagina)Oral receptive (your partner sucks your vagina/penis)Oral insertive (you suck partner’s vagina/penis)None of the aboveHave you gone through any of the following in the past 6 months?Sexually abusedStabbedBittenScratchedNone of the aboveHave you experienced/noticed any or many of the following?Weight loss of more than 5 kg over 3 monthsPersistent cold and flu in the past 6 monthsPersistent diarrhea and fatigue in the past 6 monthsRecurring night sweats in the past few monthsWhite patches in mouthBad breathSore throatUlcersDifficulty in eatingDry coughWet cough for more than 3 weeks in the past 1 yearBlood in cough in the past 1 yearPersistent fever or chills for no known reasons in the past 1 yearPersistent shortness of breath or chest pain in the past 1 yearHave you experienced/noticed any or many of the following?Genital warts (small bumps on genitals)Genital herpes (genital pains or sore genitals and open sores on genitals)Gonorrhea (bacterial infection: white or yellow liquid visible in genital region)Syphilis (rash on the body or painless sore on genitals, rectum, or mouth)Gonococcal (painful urination and abnormal discharge from penis or vagina)None of the above

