### Data Analysis

The study endpoints for this trial are concerned with the proportion for concordance of the participants’ risk assessment score with the confirmatory test results.

An interim analysis of the results will be reviewed after visit 1 has been completed. All the recorded risk behavioral scores will be analyzed for any correlation between HIV testing outcomes.

In addition, the analysis plan will include an evaluation performed at visit 2, identifying cases where an initial nonreactive test (at visit 1) has resulted in a change to a reactive test result (at visit 2).

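### At visit 2 the last-HIV-test item records the study's own visit-1 test, and part of the 6-month and 1-year look-backs precedes that negative test, so the visit-2 score can shift because of the study itself

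*Protocol article*

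**What the plan says.** The Design section sets the interval and the population for the second visit: "If a participant tests negative, they will be found eligible for visit 2, which will occur 3 months after visit 1". It then says: "At visit 2, the participant will follow the same process as that completed at visit 1". The first step of that process is "completing a series of behavioral questions on an application system without the assistance of trained staff".

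Subject Tool Evaluation lists one question set, with no separate visit-2 version:

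- The item on the most recent HIV test offers 0-3 months, 3-12 months, more than 12 months, or never tested.
- Sexual activities, abuse/injury and two symptom options look back 6 months.
- Four symptom options (wet cough, blood in cough, fever or chills, shortness of breath or chest pain) look back 1 year.
- The partner item asks about people "with whom you had sex in the past 3 months".
- The condom item, the sexually transmitted infection item and several symptom options have no stated look-back.

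On use of the scores, the Abstract (Methods) says: "All risk assessment scores will be used to calculate the reliability of the machine-guided tool". Data Analysis adds a further evaluation once follow-up is done: "identifying cases where an initial nonreactive test (at visit 1) has resulted in a change to a reactive test result (at visit 2"). Skewed Data says the follow-up test will be compared with the predictive ability of the phase-1 model, but does not say which visit's answers supply the score.

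**The concern.** The first visit includes an HIV test, and one item in the tool asks how recently the participant was tested. Repeating the tool 3 months later means the study has changed the true answer to its own question. A person who had never tested before enrolment must now truthfully report a recent test, although nothing about that person's own testing behaviour has changed.

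The longer look-backs raise a related, weaker issue. Part of the period they cover was already reported at visit 1 and was followed by a negative test, whereas the visit-2 HIV result is used to detect what happened between the visits.

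At stake is the interpretation of any analysis that sets the visit-2 score against the visit-2 result, or that compares a participant's two scores. The failure rate is exposed too. Error and Failure Rates defines a failure as a high score with negative tests at both visits, without saying which visit's score counts, so a study-induced shift at visit 2 could change who is counted.

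**Working it through.** The article gives no figure for this overlap, so there is nothing to reproduce. The check uses the listed windows and the planned interval.

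**Inputs.** Interval between visits g = 3 months (Design). Look-back windows W = 3, 6 and 12 months (Subject Tool Evaluation).

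**Testing item.** With no test outside the study since visit 1, the most recent test at visit 2 was g months ago.

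- Never tested: cannot be true for any attendee.
- More than 12 months: cannot be true, because g is about 3.
- 0-3 months: true if g is 3 or less.
- 3-12 months: true if g is 3 or more.

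Two of four categories are therefore unavailable to all visit-2 attendees. At exactly g = 3 both remaining categories are true. Attending slightly early gives one, and slightly late gives the other. Someone who tested elsewhere after visit 1 would report that test instead, and for that person the item still reflects their own behaviour.

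**Look-back windows.** Share of a window that lies before visit 1 = max(0, W − g)/W.

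| Window | Items | Share before visit 1 at g = 3 |
|---|---|---|
| 3 months | sexual partners | (3 − 3)/3 = 0% |
| 6 months | sexual activities, abuse/injury, two symptom options | (6 − 3)/6 = 50% |
| 12 months | four symptom options | (12 − 3)/12 = 75% |

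**Sensitivity to timing.** The article states no visit window. If attendance ranged from 2.5 to 4 months (an assumption):

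- 6-month share: from (6 − 2.5)/6 = 58% down to (6 − 4)/6 = 33%.
- 12-month share: from (12 − 2.5)/12 = 79% down to (12 − 4)/12 = 67%.
- Partner item: (3 − 2.5)/3 = 17% at the early end, and 0% from 3 months onward.

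**Effect on the score.** This would need the weight of each item, which the article does not give. Neither size nor direction can be computed.

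**The case against.** Several points on the other side have force.

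- **Overlap is not itself an error.** A fixed-window instrument asked twice at 3 months will overlap. Nothing in the article says the visit-2 score should cover only the time between visits. This stands, and it makes the look-back point secondary.
- **The look-back point is narrow.** A reader might infer that the 6-month and 1-year windows mostly re-count time before visit 1. The figures do not support that for the 6-month windows, which hold the sexual-activity and abuse/injury questions and are split exactly in half. The 75% share applies only to four options in one symptom list.
- **No effect on the score is shown.** A reader might infer that visit-2 scores are biased. Without weights, the article supports only that they can shift.
- **The relabelled answer is true.** By visit 2 the person has been tested. But the item then separates attendees by attendance day rather than by their own testing habits, unless they tested elsewhere.
- **Pre-study history is not lost.** Demographic and Health Data Collection records the approximate date of the last HIV test. This stands, and it makes the repair cheap.
- **Predictive evaluation is already planned.** Skewed Data refers to the phase-1 model, and analyses are run after each visit. Neither statement says which visit's score is set against the visit-2 result. Equally, the article does not state that the two visits will be pooled, and its use of the word reliability need not mean agreement between visits. Neither reading should be presumed.
- **The question set may not be unchanged.** That it is repeated as listed is inferred from the same-process sentence and the single list. Figure 2 is not shown, and a fuller protocol could contain visit-2 wording. The inference is the plain reading, but it remains an inference.

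**Conclusion.** The point holds in limited form. Its firm part is the testing-history item: for every visit-2 attendee two of four answers are ruled out by the study's own test, and the other two meet at the planned interval. That needs no assumption about weights, only that the listed questions are repeated and that attendance is near 3 months.

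The supporting part is that, at exactly 3 months, 50% of each 6-month window and 75% of the 1-year window for four symptom options precede the negative visit-1 test. The partner item is unaffected at that interval, and the items without a stated window cannot be assessed.

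The visit-2 score can therefore move because of study testing. How far it moves, in which direction, and whether any endpoint changes materially are unknown. This is worth correcting because the affected score may be set against the visit-2 HIV result and the repair is inexpensive. It does not show that the study's results are invalid.

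**What to change.** 1. **Testing-history item at visit 2.** Score it with study tests excluded. Ask about HIV tests outside the study, carry forward the pre-study date of last test already recorded under Demographic and Health Data Collection, or do both. Carry forward the date rather than the visit-1 category: someone last tested between 9 and 12 months before visit 1 passes 12 months by visit 2 (9 + 3 = 12).
2. **Categories.** Make them non-overlapping, for example less than 3 months and 3 to 12 months.
3. **Data Analysis.** State that nonreactive-to-reactive change at visit 2 is evaluated against the visit-1 score, which is the one taken before the interval begins. Use the visit-2 score for repeatability and usability.

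**Cost.** Items 1 and 2 are a small wording change. Data collection has begun, so the ethics committee would need to be notified, and one item would be handled slightly differently at the two visits. Carrying the recorded date forward avoids a new question. Item 3 needs only an analysis change and remains possible for data already collected. No extra participants or procedures are needed.

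Adding versions of the other items that ask about the time since the last visit is optional. It would give cleaner between-visit exposure, but it changes the instrument and lengthens the questionnaire.
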